The primary aim of this study is to assess the effects of supplemental vitamin D3 (1000 IU/daily) and calcium carbonate (1200 mg elemental calcium/day) on mammographic breast density.

Our primary hypotheses are:

1. Vitamin D3 (1000 IU/day) supplementation reduces mammographic breast density.

2. Calcium carbonate (1200 mg elemental calcium/day) supplementation reduces mammographic breast density.

Our secondary hypothesis is:

1. The combination of both vitamin D3 (1000 IU/day) and calcium carbonate (1200 mg elemental calcium/day) supplementation reduces mammographic breast density more than supplementation with calcium carbonate or vitamin D alone.

An exploratory hypothesis is:

1. The effect of supplementation with vitamin D3 on mammographic breast density will be modified by polymorphisms at the 3' end of the vitamin D receptor gene.

2. The combination of both vitamin D3 (1000 IU/day) and calcium carbonate (1200 mg elemental calcium/day) supplementation reduces mammographic breast density compared to placebo.

*10.5.3 Recruitment and Enrollment Procedures*

The parent study defines the pool of potential subjects for this study. Two *additional* exclusion criteria for this ancillary study are: a) a history of breast cancer, and b) not anticipating having a mammogram during the duration of the parent study. Subjects will be invited to participate in the Mammography Study in one of two ways:

1. Women currently being enrolled in the parent study will be invited to participate at the time of their in-person intake visit. Study coordinators will ask women to complete the mammography eligibility and intake questionnaire. Those who are eligible will be invited to participate in this ancillary study. If they are interested, the informed consent process will be carried out at this visit and documented on the informed consent form. The subject will also be asked to sign a medical release form to allow collection of their mammograms. Upon the subject’s randomization in the parent study, the study coordinator will collect the most recent screening mammogram from prior to enrollment, as well as subsequent mammograms from at least one year after enrollment into the parent study up until the end of the subject’s participation in the parent study. Subjects that consent to this ancillary study but become run-in failures in the parent study will be dropped from this study and their mammograms will not be collected.

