The primary method of statistical analysis for this ancillary study will be two-factor ANOVA or analysis of covariance (ANCOVA), to take advantage of the factorial nature of the design. This analysis will include a factor for Vitamin D (No, Yes), a factor for Calcium (No, Yes) and a Vitamin D x Calcium interaction term. The presence of a significant interaction will be assessed first and if the interaction term is statistically significant, and if this is due to the mean density for the combined Vitamin D + Calcium group being lower than the other three groups, then the secondary hypothesis will be supported and will show that both supplements synergistically reduce density more than each supplement alone. If the interaction term is not significant, then the marginal means in the factorial design will be tested using the main effect for vitamin D to test hypothesis 1, and the main effect for calcium to test hypothesis 2. (If the interaction term is significant, then main effects will still be tested, recognizing that there are differential effects). If group differences are observed, we will then conduct exploratory analyses to determine whether supplementation leads to a change in breast density (i.e., between pre-randomization mammogram and post-randomization mammogram). In addition, in exploratory analysis we will also use ANOVA to test the hypothesis that mammographic breast density is significantly lower in women randomized to the combination of vitamin D plus calcium compared to the placebo group.

We will also use ANOVA to test the exploratory hypothesis that the effect of supplementation with vitamin D on mammographic breast density is modified by polymorphisms at the 3' end of the vitamin D receptor gene. For this analysis, we will include a dichotomous variable to represent the presence or absence of the polymorphism, a dichotomous variable for vitamin D supplement (yes vs. no), and a cross-product term of these two variable. We will also include a dichotomous variable for calcium (yes vs. no) is in the above analyses calcium is found to be significantly associated with breast density.

Since all statistical tests are based on a priori hypotheses and are done within the context of the ANOVA or ANVOCA models, there will be no adjustment for multiple testing in either the analysis or sample size calculations.

**Power/Sample Size Considerations**.

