Using a two-tailed test with an =0.05, and 80% power, we computed the minimal detectable difference in mean percent breast density for each of the comparisons as described for each of the primary and secondary aims below.

Primary Aim 1: Our first primary aim is to determine if supplementation with vitamin D reduces mammographic breast density. For this comparison of vitamin D versus no vitamin D we expect 384 (317 + 67) women per comparison group. This sample size will have 80% power to detect an effect size of 0.20, where effect size is defined as the mean difference in mammographic density between the vitamin D and no vitamin D groups, divided by the within group standard deviation (assumed to be the same for both groups). The units for the mean and standard deviation are percent breast density denoted by ‘%’. In a large cross-sectional study of primarily Caucasian women aged 40-93 years, percent breast density was determined by analyzing mammograms (Vachon et al, 2002). In that study, a standard deviation of 15% was observed. Given the similar age range of women in that study and our proposed study, we based our power estimates assuming a standard deviation of 15%. Therefore, the minimal detectable difference between the vitamin D groups is 3% (=.20 x 15).

Primary Aim 2: Our second primary aim is to determine if supplementation with calcium carbonate (calcium) reduces mammographic breast density. For this comparison of calcium versus no calcium, we expect 634 (317 + 317) women in the calcium group and 134 women (67 + 67) in the no calcium group. This sample size will have 80% power to detect an effect size of 0.27. Assuming a standard deviation of 15% for percent breast density, the detectable difference between the calcium groups is 4.0% (=.27 x 15).

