Secondary Aim 1: Our secondary aim is to determine if supplementation with both vitamin D and calcium reduces mammographic breast density more than supplementation with calcium alone or with vitamin D alone. This vitamin D by calcium interaction reflects the vitamin D effect in the absence of calcium (67 vs 67 women) compared with the vitamin D effect in the presence of calcium (317 vs 317 women). These sample sizes will have 80% power to detect an effect size of 0.54. Here, effect size is defined as (vitamin D effect in the absence of calcium – vitamin D effect in the presence of calcium)/within group standard deviation (grouping is the 4 treatment combination groups and the standard deviation is assumed to be the same for the 4 groups). Assuming a standard deviation of 15% for percent breast density, there is 80% power to detect a vitamin D vs no vitamin D mean difference in the presence of calcium that is 8% higher than the vitamin D vs no vitamin D mean difference in the absence of calcium. For example, if the mean percent density in the 67 women not on vitamin D and not on calcium is 30%, and the mean percent density in the 67 women on vitamin D and not on calcium is 27% (vitamin D effect in the absence of calcium is 30 – 27 = 3%), and if the mean percent density in the 317 women not on vitamin D but on calcium is 26%, then there is 80% power to detect a mean percent density in the 317 women on vitamin D and on calcium of 15% (vitamin D effect in the presence of calcium is 26 – 3 – 8 = 15%).

10.6 *Kidney Function with Vitamin D/Calcium*

This sub-study will investigate the effect of vitamin D and calcium supplementation on measures of renal function and blood pressure.

Subjects in the parent study who consent to this ancillary study will undergo the following additional procedures at their end of treatment (EOT) visit (either Year 3 or Year 5 EOT):

- Urine collection for measuring microalbuminuria
- Blood pressure measurement
- An additional vial of blood will be collected for measuring markers of kidney function (see below)

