### 13.5 Statistical Analysis

All analyses will be conducted according to the principle of intention to treat. The analysis population will consist of all randomized patients, with patients being grouped according to randomized treatment assignment regardless of whether this treatment was actually delivered.

To address our primary hypotheses, the primary statistical analysis will use contingency tables and standard 2 tests to compare adenoma occurrence between treatment groups. There will be three primary comparisons: 1) vitamin D versus no vitamin D, and 2) calcium versus no calcium and 3) vitamin D + calcium versus calcium alone. Comparison 1 will collapse numbers of subjects across calcium supplementation groups to assess the marginal effect of vitamin D. Comparison 2 will collapse numbers of subjects across the vitamin D supplementation groups to assess the marginal calcium effect and will exclude women who do not consent to randomization in the calcium component of the study. Comparison 3 will focus only on subjects taking calcium; no collapsing is necessary. Effects will be summarized using risk ratios rather than odds ratios to improve interpretation. Two-sided significance levels of 0.05 will be taken to denote statistical significance.

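### The mammography study's secondary hypothesis is that the combination beats each single agent, but it is judged by the interaction test, which tests synergy and misses a purely additive benefit

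*Protocol*

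**What the plan says.** Protocol 10.5.2 gives the secondary hypothesis: the combination "supplementation reduces mammographic breast density more than supplementation with calcium carbonate or vitamin D alone". The Secondary Aim 1 paragraph under Power/Sample Size Considerations in 10.5.5 repeats that aim in similar words. Its next sentence treats the aim as an interaction: "This vitamin D by calcium interaction reflects the vitamin D effect in the absence of calcium". That effect is set against the one seen when calcium is given. Power is stated only for that contrast: 80% at 0.54 SD, or 8 points with an SD of 15.

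The decision rule is in 10.5.5, Statistical Analysis. It has two parts. First, the interaction term must reach significance. Second, the reason for this must be the position of the combined arm: "if this is due to the mean density for the combined Vitamin D + Calcium group being lower than the other three groups". The plan's reading of a result that meets both parts is definite: "then the secondary hypothesis will be supported and will show that both supplements synergistically reduce density more than each supplement alone". If the interaction is not significant, the two main effects are tested for primary hypotheses 1 and 2; they are also tested if it is significant. The only other named contrast involving the combined group is exploratory, against placebo. No test of the combination against calcium alone, or against vitamin D alone, is given.

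The parent trial treats its matching hypothesis 3 differently. Section 13.5 compares vitamin D plus calcium directly with calcium alone: "Comparison 3 will focus only on subjects taking calcium; no collapsing is necessary".

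**The concern.** The hypothesis as worded is a pair of simple comparisons: the combined mean is below the calcium-alone mean and below the vitamin-D-alone mean. Neither requires synergy. The null hypothesis of the interaction test is that the two effects add, which is a different statement. If each agent lowers density and the effects add, the combination does beat each agent and the interaction is exactly zero. A rule that depends on the interaction will then leave a true hypothesis unsupported in nearly every trial, and the stated 80% power does not apply to that hypothesis.

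There is a smaller gap on the other side. The requirement that the combined mean be lower than the other three has no test attached. When the combination and calcium alone have equal true means, chance alone puts the combined mean below the calcium-alone mean half the time.

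Section 10.5.1 says the results could inform the design of a breast cancer chemoprevention trial, so the formal verdict on the combination matters.

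**Working it through.** **Inputs (Protocol 10.5.5).** Women per cell: placebo 67, vitamin D alone 67, calcium alone 317, both 317. SD 15 points. "Using a two-tailed test" with alpha "0.05, and 80% power". Example means: placebo 30, vitamin D alone 27, calcium alone 26, so effects of 3 and 4 points. All other sets of means below are assumptions. The combined arm's 317 consists of 67 full-factorial women and 250 two-arm women.

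**1. Reproduce the stated figure.** The interaction contrast is (both − calcium) − (vitamin D − placebo).
- SE = 15 × √(2/67 + 2/317) = 15 × 0.1902 = 2.85 points.
- Detectable at 80% power = (1.960 + 0.842) × 0.1902 = 0.533 SD = 7.99 points.
- Power at 0.54 SD is 81%. The stated 0.54 SD and 8 points are correct for an interaction.

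**2. Make the protocol's example additive.** The combined mean is 30 − 3 − 4 = 23, and the interaction is (23 − 26) − (27 − 30) = 0. The hypothesis is true, since 23 is below both 26 and 27. The protocol's own worked example needs a combined mean of 15, 11 points below calcium alone, for 80% power.

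**3. Power of direct contrasts at 30/27/26/23.**
- Both v calcium alone: SE = 15 × √(2/317) = 1.191; 3/1.191 = 2.52; power 71%.
- Both v vitamin D alone, full-factorial women only: SE = 15 × √(2/67) = 2.592; 4/2.592 = 1.54; power 34%.
- Both v vitamin D alone, all combined-arm women: SE = 15 × √(1/67 + 1/317) = 2.017; 4/2.017 = 1.98; power 51%.

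**4. How often each approach declares support when effects are additive (simulated arm means).** The rule is coded as a significant interaction with the combined mean numerically lowest.

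| Additive effects (vitamin D, calcium) | Rule | Rule, synergistic direction only | Both contrasts, 67 v 67 for the second | Both contrasts, all combined-arm women |
|---|---|---|---|---|
| 3, 4 (protocol) | 4.1% | 2.5% | 27% | 40% |
| 6, 6 (assumed) | 5% | 2.5% | 64% | 84% |

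Larger effects do not help the rule. It stays at or below the test's alpha, because the quantity tested is zero.

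**5. Support when adding vitamin D to calcium changes nothing (assumed means: placebo/vitamin D/calcium/both).**

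| Means | Situation | Rule |
|---|---|---|
| 30/30/26/26 | vitamin D inert | about 2% |
| 30/27/26/26 | vitamin D works alone, adds nothing to calcium | about 1% |
| 30/33/26/26 | vitamin D alone raises density by 3 | 13% |
| 30/34/26/26 | raises by 4 | 20% |
| 30/38/26/26 | raises by 8 | 44% |

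The two direct contrasts, both required, declare support in at most about 2.5% of trials in each of these rows. One qualification concerns the wording of the rule. If the clause about the lowest mean is read as a bare numerical ordering, whatever the sign of the interaction, a large sub-additive pattern such as 30/22/18/18 also triggers it (35%). If the interaction must point towards synergy, that case falls to about 0%.

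**6. Detectable differences for the direct contrasts at 80% power.**
- 317 v 317: 2.802 × √(2/317) = 0.22 SD = 3.3 points.
- 67 v 67: 2.802 × √(2/67) = 0.48 SD = 7.3 points.

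**The case against.** The strongest reply is that synergy was intended and the hypothesis is only loosely worded. Section 10.5.1 mentions synergistic effects, the rule itself uses the adverb, and the effect-size definition, power and worked example are all those of an interaction. On that reading, 5% under additivity is the type I error of a correctly specified test, not a lack of power. This has real support. It does not remove the mismatch, because 10.5.2 and the opening of Secondary Aim 1 state superiority to each single agent, so some text has to change either way.

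A second reply is that the main effects are tested whatever the interaction shows, and under additivity two beneficial main effects imply that the combination beats each agent. At 3 and 4 points, both pooled main effects (384 v 384 and 634 v 134) are significant in about 63% of trials. This also stands: the evidence would be reported. But the inference assumes additivity, and the calcium comparison draws in two-arm women who were not randomised to calcium. The plan also assigns the main effects to hypotheses 1 and 2, not to this one.

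Third, false support at a raised rate in the synergistic direction needs vitamin D alone to raise density, which is the opposite of primary hypothesis 1. Such an interaction is arguably not due to a low combined mean. This is fair and limits that part of the point.

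Finally, the direct contrasts are not strong either: at the protocol's effects only 27% of trials succeed on both with 67 v 67. That is a limit of the sample and should be stated.

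**Conclusion.** The point holds as a mismatch between hypothesis and test. Under additive effects the stated hypothesis is true, yet the rule supports it in at most about 5% of trials: 4.1% at the protocol's own 3 and 4 points, 2.5% in the synergistic direction. That the interaction is zero follows from its definition and needs no assumed effect size. The comparison figures (71% for combination v calcium alone; 27% or 40% for both contrasts) rest on the protocol's cell sizes, its SD of 15 and its example means.

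Three stronger readings are not supported. A reader might infer that the rule readily declares success when vitamin D adds nothing to calcium. At the protocol's effect sizes it does so in only about 1% to 2% if vitamin D is inert or works only without calcium; the 13% to 44% range needs an assumed rise of 3 to 8 points on vitamin D alone, which nothing in the document suggests. A reader might infer that an additive benefit would go unreported; the main effects would still show it indirectly. A reader might infer that the 0.54 SD figure is wrong; it reproduces, but it describes synergy.

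This is a secondary hypothesis of an ancillary study, and no parent-trial result depends on it. It should be corrected, but it does not threaten the trial.

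**What to change.** If the hypothesis stays as worded, test it by two direct contrasts, both required:
- vitamin D plus calcium v calcium alone, using all 317 v 317, since every woman in these arms is randomised to vitamin D or not;
- vitamin D plus calcium v vitamin D alone, in full-factorial women only (67 v 67), since two-arm women could not be assigned to vitamin D alone.

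Keep the interaction as a separately labelled test of synergy with its 0.54 SD figure. In Secondary Aim 1, add the power of the direct contrasts: 80% at about 0.22 SD (3.3 points) for the first and about 0.48 SD (7.3 points) for the second, with a plain statement that the second has limited power.

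If synergy alone is intended, reword the hypothesis in 10.5.2 and the aim in 10.5.5 as synergy. Then say that a non-significant interaction will not be read as evidence that the combination is no better than either agent.

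Either route changes wording only, in 10.5.2 and 10.5.5. No new data or procedures are needed.

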**Study Design**

The goal of the parent study is to enroll 3000 total participants and to randomize 2400. Based on current recruitment rates, approximately 40% of the participants are women; therefore it is estimated that approximately 960 participants will be women. Of the women recruited we expect that 624 will be enrolled in the two-arm and 336 will be enrolled in the full-factorial study. Based on preliminary data that were collected from four study centers (NC, SC, GA and TX), it is estimated that at least 80% of women randomized will be eligible (i.e., no history of breast cancer) and will agree to participate in the mammography study.

|  | **Vitamin D** | **Calcium** | **Vit D and Calcium** | **Placebo** | **TOTAL** |
| --- | --- | --- | --- | --- | --- |
| Two-arm |  | 312 | 312 |  | 624 |
| Full-factorial | 84 | 84 | 84 | 84 | 336 |
| **Total randomized** | **84** | **396** | **396** | **84** | **960** |
| **No. of eligible women who agree to participate.** | **67** | **317** | **317** | **67** | **768** |

The design for this ancillary study is a 2 x 2 factorial design as follows:

|  | **Calcium - No** | **Calcium – Yes** | **TOTAL** |
| --- | --- | --- | --- |
| **Vitamin D – No** | 67 | 317 | 384 |
| **Vitamin D - Yes** | 67 | 317 | 384 |
| **TOTAL** | 134 | 634 | 768 |

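### Mammography study, Primary Aim 1: the weighting of the calcium strata in the vitamin D main effect is not fixed, and power at 0.20 SD is 79% or about 56% depending on it

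*Protocol*

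**What the plan says.** All of this is in Protocol section 10.5.5.

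- **Design.** "The design for this ancillary study is a 2 x 2 factorial design as follows": the table gives 67 women in each vitamin D group without calcium and 317 in each with calcium, so the vitamin D margins are 384 and 384.
- **Model.** The primary method is a two-factor ANOVA or ANCOVA with a vitamin D factor, "a factor for Calcium (No, Yes) and a Vitamin D x Calcium interaction term". The interaction is examined first. If it is not significant, "the marginal means in the factorial design will be tested using the main effect for vitamin D to test hypothesis 1". If it is significant, the main effects are tested all the same. No step removes the product term, and no sum-of-squares type or weighting of marginal means is named.
- **Power.** "Using a two-tailed test" at alpha 0.05 and "80% power, we computed the minimal detectable difference in mean percent breast density for each of the comparisons". For Primary Aim 1: "For this comparison of vitamin D versus no vitamin D we expect 384 (317 + 67) women per comparison group", and "This sample size will have 80% power to detect an effect size of 0.20". The effect size is the mean difference between the two vitamin D groups divided by the within-group SD. On the SD itself, "we based our power estimates assuming a standard deviation of 15" percentage points, which gives a detectable difference of 3 points.

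**The concern.** The layout is very unequal on calcium: 134 women without it and 634 with it. In such a layout the vitamin D marginal means can be formed in two ways. Weighted by cell size, the no-calcium stratum counts for 134/768 = 17%. Weighted equally, as in the usual Type III main effect of a model with interaction, it counts for 50%. Both are compatible with the analysis text, but only the first matches the power calculation.

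At stake is the power of the first primary hypothesis of this ancillary study, for the factor to which every woman is randomised. The estimate is also at stake. Main effects are to be tested even under a significant interaction, and the two weightings then estimate different quantities. Left open, the choice could be made after the data are seen.

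**Working it through.** **Inputs (10.5.5).** Two-sided alpha 0.05, target power 80%, SD 15 points, vitamin D effect 0.20 SD; cells 67/67 (no calcium) and 317/317 (calcium). Effects and standard errors are in SD units. Power ≈ Φ(effect/SE − 1.96); detectable effect at 80% power = (1.96 + 0.84) × SE.

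**1. The plan's own figure.** Pooled 384 vs 384:
- SE = √(2/384) = 0.0722
- Power at 0.20 = Φ(0.20/0.0722 − 1.96) = 0.791 (noncentral t: 0.790)
- Detectable effect = 0.202 SD, or 3.0 points

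The stated 80% is reproduced.

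**2. Size-weighted main effect with the interaction in the model.** Let d₀ and d₁ be the vitamin D differences without and with calcium. The estimate is (67·d₀ + 317·d₁)/384, with SE = √(2/384) = 0.0722 and power 79%. Vitamin D is 1:1 within each calcium level, so cell frequencies are proportional and vitamin D is orthogonal to calcium. The Type I and Type II tests therefore equal the pooled comparison even with the product term retained. In one simulated data set, F was 11.03 for Type I, Type II and the weighted marginal difference, against 9.65 for Type III.

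**3. Equally weighted main effect (Type III).** The estimate is (d₀ + d₁)/2:
- Variance = 0.25 × (2/67 + 2/317) = 0.00904, against 2/384 = 0.00521, which is 74% larger
- SE = 0.0951
- Power at 0.20 = Φ(0.20/0.0951 − 1.96) = 0.557 (noncentral t: 0.556)
- Detectable effect = 0.266 SD; × 15 = 4.0 points

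A simulation of 20,000 trials with these cell sizes and no interaction gave 55.7% for equal weighting and 78.9% for size weighting with the interaction retained.

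**4. The other two stated figures.**
- Calcium: SE = √(1/134 + 1/634) = 0.0951; power at 0.27 = 0.811. The SE is the same under either weighting, because the vitamin D groups are equal in size.
- Interaction: SE = √(2/67 + 2/317) = 0.190; power at 0.54 = 0.811.

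Both reproduce, so only Primary Aim 1 depends on the weighting.

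**5. Effect on the estimate.** In the protocol's own interaction example, vitamin D lowers density by 3 points without calcium (30 to 27) and by 11 with it (26 to 15). Equal weighting gives (3 + 11)/2 = 7.0 points. Size weighting gives (67 × 3 + 317 × 11)/384 = 9.6 points. The plan does not say which of these answers hypothesis 1.

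**The case against.** The strongest reply is that the protocol already points to the size-weighted reading, and then nothing stated is wrong. The factorial table shows vitamin D margins of 384 and 384. The effect size is defined as the difference between the whole vitamin D and no-vitamin-D groups. Section 13.5 forms the parent trial's marginal vitamin D effect by collapsing over calcium. Nothing in 10.5.5 mentions Type III, effect coding or least-squares means. On that reading the analysis and the power agree at 79%. The reply adds that sum-of-squares type is a detail normally left to a statistical analysis plan, which is not at hand here.

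Most of this stands, and it rules out a stronger reading that a reader might infer: that keeping the interaction in the model brings power down to 56%, so that the stated 80% is wrong. The documents do not support this. The product term costs essentially nothing when vitamin D is balanced within each calcium level, and equal weighting is nowhere prescribed. Nor does the agreement of the calcium figure with the ANOVA show that Type III was intended, since that figure is the same either way.

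The reply does not remove the point altogether. Section 10.5.5 itself fixes the model, the order of testing and the power. It puts the interaction in the model, never takes it out, and tests main effects even when the interaction is significant. An analyst who reported the usual Type III main effect would be following the text and would miss the power stated in the same section.

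**Conclusion.** The point holds as an ambiguity with a measurable consequence, not as an error in the stated power. Power for Primary Aim 1 at 0.20 SD is 79% if the vitamin D main effect is size-weighted and about 56% if the calcium strata are weighted equally. The detectable effect at 80% power is 0.20 SD (3.0 points) or about 0.27 SD (4.0 points) respectively. The wording leans toward the first reading but does not settle it.

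These figures assume the planned cell sizes, exact 1:1 vitamin D allocation within each calcium level, a common SD of 15 points and, for power, the same vitamin D effect in both strata. Covariate adjustment or uneven participation would make the equality of the Type I, Type II and pooled tests approximate rather than exact.

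The matter is confined to this ancillary study. Its calcium and interaction figures stand, and the parent trial's sample size and primary analysis are not touched.

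**What to change.** Add one sentence to the statistical analysis text of 10.5.5: hypothesis 1 is tested by the size-weighted vitamin D effect (additive model with vitamin D and calcium, or the Type II test), and the model with the product term is used for the interaction test. Say also that this estimate is weighted 634/768, about 83%, toward women taking calcium, and repeat this when the result is reported. That is the price of the size-weighted choice: it says little about women not taking calcium.

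If equally weighted marginal means are intended, keep the analysis, name the weighting, and restate the minimal detectable difference for Primary Aim 1 as about 0.27 SD (4.0 points).

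Either change is a matter of wording. Neither alters recruitment, data collection or the other power figures.

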As in our previous trials, subsequent, more detailed, multivariate analyses will consist of generalized linear models for binary data to estimate adjusted risk ratios (i.e., using a log link function) and confidence intervals for neoplastic polyp occurrence among the treatment groups. We anticipate that the distribution of relevant covariables will be approximately balanced across the treatment groups because of random assignment in a relatively large sample. Some imbalances may occur, making it necessary to critically examine possible covariates. These include number of previous adenomas, size of qualifying adenomas, selected dietary variables (e.g., calcium intake) or sunlight exposure. The distribution by treatment group of these covariates (for the whole sample as well as by center) will be assessed. For those variables with large and systematic imbalances, stratified analyses will be employed to confirm or modify the preliminary analyses. Factors used to stratify the randomization (center, planned follow-up interval, full factorial participation) will be included as covariates. We will also use these models to evaluate the interaction between vitamin D supplementation and calcium supplementation. The interaction effect will be tested by including the appropriate product term in the model. This interaction analysis will include only those subjects enrolled in the full factorial design (i.e., women wishing to take calcium supplements will be excluded). We do not expect differential treatment effects according to age, gender or race, but we will consider the corresponding interactions for the treatments.

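### Mammography sub-study: the calcium main effect (634 vs 134 women) is a largely non-randomised comparison, and its randomised part detects about 5.1 points, not 4.0

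*Protocol*

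**What the plan says.** Section 10.5.5 (Study Design) takes 624 two-arm and 336 full-factorial women, applies 80% participation, and sets the result out as a two-by-two table: "The design for this ancillary study is a 2 x 2 factorial design as follows". The calcium column holds 317 + 317 women from both components; the no-calcium column holds 67 + 67, all full-factorial.

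The analysis is a two-factor ANOVA or ANCOVA with vitamin D, calcium and their interaction. The calcium main effect tests primary hypothesis 2. No factor separates the two components. The same section expects confounder imbalance to be small because the study is randomised.

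The power statement for Primary Aim 2 reads "we expect 634 (317 + 317) women in the calcium group and 134 women (67 + 67) in the no calcium group", then "This sample size will have 80% power to detect an effect size of 0.27" and "Assuming a standard deviation of 15% for percent breast density, the detectable difference between the calcium groups is 4.0% (=.27 x 15".

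Sections 5.2 and 13.3 say that two-arm women all take calcium and are randomised only to vitamin D or not. In the parent trial, sections 3.1 and 13.5 remove them from the calcium comparison, and section 13.5 also removes them from the interaction analysis: "i.e., women wishing to take calcium supplements will be excluded".

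**The concern.** Most women counted as calcium-treated were not allocated to calcium; they asked for it. Nobody in the comparator made that choice. The pooled contrast therefore mixes any effect of calcium with any difference in density between women who insist on calcium and women who will forgo it.

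The protocol gives reasons to expect such a difference. Section 5.2 justifies the two-arm option by calcium recommendations for post-menopausal women and their common supplement use. Section 10.5.1 lists age, reproductive factors, BMI and hormone therapy as associated with density, and names menopausal status among the confounders to control. Randomisation cannot be expected to balance these factors across a contrast it did not create, so the reassurance in 10.5.5 does not apply to this test.

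At stake is one of the sub-study's two primary hypotheses, whose result section 10.5.1 hopes will inform a breast cancer chemoprevention trial.

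**Working it through.** **Inputs.** Two-sided alpha 0.05 and 80% power (10.5.5, Power/Sample Size: "0.05, and 80% power, we computed the minimal detectable difference in mean percent breast density"), so z = 1.960 + 0.842 = 2.802. SD 15 points. Randomised women: 624 two-arm; 336 full-factorial, 84 per arm. Participation 80% in every cell, as in the protocol's table.

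**Who is in the calcium group**
- Two-arm women: 624 × 0.8 = 499.2, about 499. Share: 499/634 = 79%.
- Women randomised to calcium: (84 + 84) × 0.8 = 134.4, about 134, or 21%.
- No-calcium group: (84 + 84) × 0.8 = 134.4, about 134, all full-factorial.

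**The protocol's figure, reproduced.** Detectable effect = 2.802 × √(1/634 + 1/134) = 0.266 SD; × 15 = 4.0 points. Power at 0.27 SD is 81%. The arithmetic is right for those group sizes.

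**The randomised comparison (134 vs 134)**
- Detectable effect: 2.802 × √(2/134) = 0.342 SD; × 15 = 5.1 points.
- Power at 0.27 SD: 0.27/√(2/134) = 2.21; 2.21 − 1.96 = 0.25; Φ(0.25) = 0.60.
- Women needed for 80% power at 0.27 SD: 2 × (2.802/0.27)² = about 216 per group.

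Adding a component term to a main-effects model does not recover the lost precision for calcium. Calcium does not vary within the two-arm component, so its effect is then estimated from full-factorial women alone.

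**How much selection could matter (illustration; the documents give no component difference).** Suppose calcium has no effect and two-arm women differ in mean density from full-factorial women by d SD. The bias in the pooled contrast is 0.79 × d, and its standard error is √(1/634 + 1/134) = 0.095 SD.
- d = 0.1 (1.5 points): bias 0.079 SD; the nominal 5% test rejects about 13% of the time.
- d = 0.2 (3 points): bias 0.157 SD; it rejects about 38% of the time.

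**The interaction.** Section 10.5.5 sets the vitamin D effect without calcium (67 vs 67) against the effect with calcium, "compared with the vitamin D effect in the presence of calcium (317 vs 317 women"). Vitamin D is randomised within both components, so a difference in density level between components cancels within each vitamin D contrast.
- All women, with a component term: 2.802 × √(2/67 + 2/317) = 0.533 SD; × 15 = 8.0 points (stated: 0.54 SD, 8 points).
- Full-factorial women only: 2.802 × √(4/67) = 0.68 SD, about 10.3 points.

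**The case against.** The strongest defence is that the plan anticipates confounding. Section 10.5.5 compares demographics, hormone use, menopausal status and BMI across groups, adds covariates where differences appear, and names ANCOVA. A pre-randomisation mammogram is also collected. This is relevant mitigation for the measured factors, but it does not restore randomisation. Adjustment is conditional on an observed difference and cannot reach unmeasured factors. The primary analysis uses the post-treatment mammogram; change from the earlier one is exploratory and follows only if groups differ. Section 5.2 also expects two-arm women to be continuing calcium, so some of their earlier mammograms may already reflect its use.

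A reader might go further and infer that the comparison is purely observational and has no valid power. That overstates it. About 21% of the calcium group was randomised against the 134 controls, and the randomised comparison has about 60% power at the stated effect.

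A reader might also infer that the interaction test loses the protection of randomisation and that its 8 points must become 10.3. The documents do not support this, because both vitamin D effects being compared are randomised contrasts. What remains is narrower: calcium status is tied to component, so the interaction is biased if component itself modifies the vitamin D effect. In addition, the extra requirement for declaring synergy, that the combined group's mean be lower than the other three, does compare density levels.

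**Conclusion.** The point stands for the calcium main effect. As planned, primary hypothesis 2 of the mammography sub-study rests on a contrast in which about 79% of the calcium group chose calcium, with no counterparts among the controls and no component term. This conflicts with the parent trial's treatment of the same women and with the sub-study's own appeal to randomisation. The detectable difference for the randomised comparison is about 5.1 points rather than 4.0, with about 60% power at 0.27 SD.

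The counts rest on the protocol's equal 80% participation in both components; the power figures also use its SD of 15 points and a normal approximation. The interaction's 8 points is acceptable with a component term if component does not modify the vitamin D effect. The sub-study's vitamin D hypothesis is a randomised comparison in all women. The parent trial's calcium and interaction analyses already exclude two-arm women, so none of its conclusions is affected.

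**What to change.** In section 10.5.5:

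1. Test the calcium main effect in full-factorial women only (about 134 vs 134), and restate its 80%-power detectable difference as about 0.34 SD, or 5.1 points.
2. Label any calcium contrast that pools in two-arm women as non-randomised and supportive.
3. Keep the vitamin D main effect in all women, with component (full factorial or two-arm) as a factor.
4. For the interaction, choose one approach in advance: all women with a component term, keeping about 8 points and stating the assumption that component does not modify the vitamin D effect; or full-factorial women only, as section 13.5 does, with about 10.3 points.
5. Limit the statement that confounder differences will be small to contrasts that randomisation created.

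The cost is wording and a less favourable stated figure for calcium. No new data are needed.
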